### Randomization and allocation concealment

Using a stratified block randomization method, 56 eligible patients will be randomly allocated to the CBT or placebo groups in a 1:1 ratio in blocks of 4. Random numbers will be generated by a computerized random-number generator using the block-randomization method of a software program (R 3.2.2) for sequence generation by an independent statistician. The randomization lists will be concealed in a lightproof sealed envelope. The sealed envelopes will be kept by the independent statistician of the study. Participants, investigators and outcome assessors will be blinded to the treatment allocation throughout the course of the study.

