All drugs are concealed in uniform packages with the same labels in the Jeonnam Biofood Technology Center and each package contains a 28-day supply. Patients in the CBT or placebo groups will take each packaged granule containing either 5 g CBT or 5 g placebo as a single dose. All drugs will be dissolved in 200 ml warm water and will be taken orally after each meal 3 times daily for 8 weeks. During the study, patients will be visited three times by the investigators. We will establish the window for visits as ±3 days. Details of the study procedures are shown in Table 2.

**Table 2 Tab2:** Detailed study procedures

Items	Screening/run-in period	Visit 1 (baseline)	Visit 2	Visit 4 (endpoint)
Week of the trial	-1	0	4	8
Demographic information-taking	+			
Informed consent form	+			
General medical history-taking	+			
Photographing the patient’s face Count of inflammatory/non-inflammatory lesions	+	+	+	+
Blood tests (AST, ALT, creatinine, serum cortisol, serum DHEA-S)	+			+
Urine pregnancy test	+		+	+
Digital infrared thermal imaging		+	+	+
Randomization & allocation	+			
Distribution of treatment or placebo		+	+	
Visual analogue scale		+	+	+
Investigator Global Assessments		+	+	+
Korean Acne Grading System		+	+	+
Pattern identification for acne	+			
Monitoring adverse events			+	+
Compliance check			+	+
Blinding check				+

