### Secondary outcomes

Secondary outcomes will evaluate the mean percentage change of non-inflammatory lesions and the total of both inflammatory and non-inflammatory lesions, the differences in temperatures of the DITI points on the face, Visual Analogue Scale (VAS) [score 0 (no symptoms) to 100 (severe symptoms)], and the Investigator Global Assessment scale for Facial Acne Vulgaris (IGA; after evaluation from score 0 (clear) to 4 (severe)) [10] from baseline to the end of the trial (at 8 weeks) between CBT treatment and the placebo control groups. Serum cortisol and dehydroepiandrosterone-sulfate (DHEA-S) will be assessed using clinical laboratory tests at weeks 0 (baseline) and 8 (end of the trial).

VAS and IGA will be checked every session from baseline (just before randomization) through the 8 weeks after randomization. A Lumix DMC-LX2 digital camera (Panasonic, Osaka, Japan) will be used to photograph the front and both sides of each patients face, so that the inflammatory and non-inflammatory lesions can be counted independently at weeks 0 (baseline), 4 and 8 (end of the trial) by a clinical specialist who has been in clinical practice for more 5 years. We will consider black and white head comedones to be non-inflammatory lesions and the inflammatory papules, pustules and cysts to be inflammatory lesions.

Correlations between the inflammatory lesion count and the temperatures of the DITI points at baseline, 4 weeks, and 8 weeks, and the frequency of abnormal liver and kidney function during this trial will also be secondary outcomes. Additionally, we will analyze the correlation between the temperatures of the DITI points and the severity of the Korean Acne Grading System (KAGS) at baseline and the end of the trial (at 8 weeks). Finally, we will analyze the success rate of blinding between the actual treatment and the perceived treatment allocations.

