### Baseline data and outcome data

An independent *T* test will be performed for comparison of the baseline values between the CBT and placebo groups. The independent *T* test will be used to examine the mean percentage change of the inflammatory/non-inflammatory lesion counts, the differences in the temperatures of the DITI points on the face, sebum level, serum cortisol, DHEA-S, VAS, and IGA at baseline and at the end of the trial (at week 8) between the CBT treatment and placebo control groups. Safety tests (AST, ALT and creatinine) will be analyzed using the independent *T* test at screening and at the end of the trial (at week 8) between the CBT treatment and placebo control groups. A repeated measured analysis of covariance (ANCOVA) test will be used to examine the percentage change of inflammatory and non-inflammatory lesions, differences in the temperatures of the DITI points on the face, VAS, and IGA at weeks 0, 4, and 8 when controlling for baseline and other covariates. The correlation between inflammatory lesion count and the facial skin superficial temperature points at baseline, 4 weeks, and 8 weeks will be examined using the Pearson correlation test. Additionally, we will analyze the correlation between the temperatures of the DITI points and the severity of the KAGS using the Pearson correlation test. The change of KAGS from baseline to week 8 will be assessed using a Chi-square test or Fisher’s exact test. All adverse events reported during the study will be included in the case report forms; the incidence of adverse events will be calculated. The percentage of subjects with adverse events in each group will be calculated and compared using a Chi-square test or Fisher’s exact test. The evaluation of blinding success between the actual treatment and the perceived treatment allocations will be performed using a Chi-square test or Fisher’s exact test.

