### Sample size

Calculation of the sample size for this trial was based on the effect size of the primary outcome, mean percent change of inflammatory acne lesion counts from baseline to week 8, reported in a previously published study [11]. The mean and standard deviation (SD) of the mean percent change of inflammatory acne lesion counts were -32.4 ± 44 and -15.1 ± 44.9 for the active treatment and control groups, respectively. To achieve 80 % power (β = 0.20), a significance level of 0.05 (α) in a two-tailed test, calculated using Cohen's d effect size values for t-tests (0.39), 28 participants, based on an estimated 20 % dropout rate, are needed for each group. This results in a required total of 56 for the trial. The mean and SD of the mean percent change of inflammatory acne lesion counts from this pilot study will be used for recalculation of the sample size for larger trials.

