## Discussion

CBT is widely used for the treatment of acne in clinical practice, but the underlying mechanism has not yet been proven. Moreover, there has been only limited research on its efficacy for inflammatory acne lesions or facial heat sensitivity. Thus, this clinical research trial was designed to provide evidence of the inhibitory effect of CBT on inflammatory acne lesions or facial heat sensitivity in patients with acne.

Our research was designed to be precise, in that we will use the placebo to maintain the double blinding of all assessors and practitioners, and have provided prior education to all practitioners. Blinding is an important scientific method in randomized controlled trials (RCT) [12]. Most RCT intend to include a double-blind design to exclude the potential influence of the natural course of the disease or any expectations of the participants and investigators [13]. In reality, because of the unique sensory and macroscopic characteristics, such as the appearance, taste and smell of herbal preparations, it is extremely difficult to prepare a placebo that is perceived to be identical to the real herbal formula while lacking any pharmacological or toxic activities [12, 13]. Consequently, we will perform an evaluation of blinding success.

The trial duration of 8 weeks was determined after considering the following issues: the lasting effectiveness time of the intervention and its tolerability by and compliance of the participants. This protocol was developed according to the guidelines for randomized controlled trials investigating Chinese herbal medicine [14] and follows the nine CONSORT checklist items for RCTs of herbal medicines [15]. We considered the main elements for conducting a high-quality RCT, such as randomization, sequence generation, allocation concealment, blinding methods, proper sample size, compliance with the protocol, and adequate outcome measures [15]. This research will provide important evidence regarding the more widespread use of CBT for the treatment of acne vulgaris.

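### Blinding is evaluated by a chi-square or Fisher test of guess against allocation; at 22 to 28 per arm a non-significant result cannot establish that blinding held

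*Protocol article*

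**What the plan says.** The article names one inferential method for the blinding check, under Baseline data and outcome data: "The evaluation of blinding success between the actual treatment and the perceived treatment allocations will be performed using a Chi-square test". The same sentence gives Fisher's exact test as the alternative.

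The Secondary outcomes section lists the quantity as an outcome: "we will analyze the success rate of blinding between the actual treatment and the perceived treatment allocations". Table 2 places the blinding check at the week 8 visit only. The Discussion gives the reason for it. In the authors' view "it is extremely difficult to prepare a placebo that is perceived to be identical to the real herbal formula", and the next step is drawn from that: "Consequently, we will perform an evaluation of blinding success".

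The general Statistical analysis plan paragraph adds that categorical data are shown as n (%) and that analyses use a 95 % confidence interval. It does not say for which blinding measure an interval would be given. The article states no significance level, power, tolerance or decision rule for the blinding test.

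The size available is set by the Sample size section: "28 participants, based on an estimated 20 % dropout rate, are needed for each group".

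**The concern.** Successful blinding means little or no association between what people guess and what they received. A test of independence takes that state as its null hypothesis. A small p-value is evidence against blinding; a large one is compatible with good blinding, and equally with moderate unblinding that the trial was too small to see. The named test therefore answers a different question from the one in the sentence that names it.

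The article gives the check real work to do. It is the stated response to the difficulty of matching a herbal placebo, and the Intervention section calls the placebo only almost identical in appearance, smell and taste. VAS is patient-reported, and IGA and the lesion counts are assessor judgements. If the final report leaned on a non-significant test, readers would be reassured about expectation bias on evidence that cannot bear it.

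**Working it through.** **Inputs from the article.** 28 per arm randomised 1:1 (Sample size; Randomization and allocation concealment). Planned dropout 20 %, so 28 × 0.80 = 22.4, about 22 per arm with a week 8 guess.

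**Assumptions, because the article gives no figures.** Each person guesses CBT or placebo, with no don't-know option. The test is two-sided at 0.05, the level stated for the primary outcome. The guess rates below are illustrative.

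**The plan's own figure.** None exists for the blinding test. The 28 per arm was set for the primary outcome and does not follow from its stated inputs: 2 × (1.96 + 0.84)² / 0.39² is about 103, or 104 per group with unrounded inputs, before dropout. That is a separate matter; here 28 serves only as the number that will be available.

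**Miss rates.** Let X be the number guessing CBT in the CBT arm and Y the number guessing CBT in the placebo arm, with X ~ Bin(n, p₁) and Y ~ Bin(n, p₂). Power is the sum of P(X = i) × P(Y = j) over all 2×2 tables with p < 0.05, and the miss rate is 1 − power. Each cell gives uncorrected chi-square / Fisher.

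| Guessing CBT, CBT arm v placebo arm | Gap (points) | Missed, n = 28 | Missed, n = 22 |
|---|---|---|---|
| 60 % v 40 % | 20 | 69 % / 78 % | 74 % / 83 % |
| 75 % v 50 % (CBT arm only unblinded) | 25 | 51 % / 61 % | 61 % / 72 % |
| 65 % v 35 % | 30 | 39 % / 50 % | 48 % / 60 % |
| 70 % v 30 % | 40 | 14 % / 21 % | 22 % / 33 % |
| 75 % v 25 % | 50 | 3 % / 5 % | 6 % / 11 % |

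By the normal approximation, the symmetric gap detected half the time is about 26 points at 28 per arm and 30 points at 22. The gap detected 80 % of the time is about 37 and 41 points.

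**One possible result.** With 22 per arm, 14 in the CBT arm and 8 in the placebo arm guess CBT, so 14/22 = 64 % are correct in each arm. Chi-square p = 0.07; Fisher p = 0.13. The gap is 6/22 = 27 points. Its standard error is √(2 × 0.636 × 0.364 / 22) = 0.145, giving a 95 % interval from about −1 to +56 points. The test flags nothing, yet the interval does not exclude serious unblinding.

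**What an index with an interval would show.** With a binary guess, Bang's index in an arm is 2p − 1, where p is the proportion guessing correctly. Its 95 % half-width is 1.96 × 2 × √(p(1 − p)/n). At p = 0.60:
- n = 28: 1.96 × 2 × √(0.24/28) = 0.36
- n = 22: 1.96 × 2 × √(0.24/22) = 0.41

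**Why the two arms must be read together.** The mean of the two indices equals the gap in the share guessing CBT. If 70 % of both arms guess CBT, the indices are +0.4 (CBT) and −0.4 (placebo), and their mean is 0. Guess and allocation are then unrelated, although the CBT arm alone would look unblinded.

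**The case against.** The strongest reply is that the article never says a non-significant result will count as success. A reader might infer that rule from the phrase about evaluating blinding success, but no sentence states it. This stands, and the point does not depend on it: whatever rule is used, the named test cannot supply positive support for blinding.

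A reader might also infer that the test misses material unblinding most of the time. The documents do not define material, and the figures do not support so general a statement. It is true for gaps of 20 to 25 points, roughly even at 30, and false at 40 or more. Nor is there a 20 % ceiling on misses for this check; that β belongs to the primary outcome.

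It would also be wrong to say that only a p-value will be reported. A success rate and n (%) are promised, so guesses by arm will probably appear. They give description, but no stated measure of uncertainty to set beside the test.

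The full protocol or analysis plan is not shown and may add an index. That is why the point rests on the test the article does name, not on an omission.

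Finally, a pass/fail margin on the index would be a poor replacement. With perfect blinding (50 % correct), the chance that both upper limits fall below an assumed margin of 0.2 is 3 % at 28 per arm and 2 % at 22; for 0.3 it is 18 % and 7 %. A rule applied to each arm alone would also fail the CBT arm when everyone guesses active. This objection stands in full, so no margin is proposed.

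Two limits apply to any method. The guess is taken at week 8, when perceived benefit can inform it. The article also does not say whose guess is recorded, and a participant's guess would not test assessor blinding.

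**Conclusion.** The point holds in this limited form. The named test is the wrong instrument for supporting a claim that blinding held, and at 22 to 28 per arm a non-significant result would say little about moderate unblinding. The sizes rest on a binary guess, two-sided 0.05 and assumed guess rates; the ranges span chi-square and Fisher and both sample sizes. Large unblinding would usually be found.

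The consequence is confined to how an ancillary secondary outcome is interpreted. No efficacy estimate changes. The improvement is worth making because it is cheap and because the article relies on this check to answer a risk it acknowledges.

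**What to change.** In Baseline data and outcome data, revise the blinding sentence so that:
- the main blinding result is the table of guesses by arm, with Bang's blinding index in each arm and its 95 % confidence interval;
- the two indices are interpreted jointly, so that both arms guessing active is not read as unblinding;
- the chi-square or Fisher test stays as a descriptive addition;
- a non-significant test will not be read as evidence of successful blinding.

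This takes a sentence or two and uses the guesses already to be collected at week 8. The cost is candour about precision: with half-widths of about 0.36 to 0.41 per arm, the report will often have to call the result inconclusive.

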### Sample size

Calculation of the sample size for this trial was based on the effect size of the primary outcome, mean percent change of inflammatory acne lesion counts from baseline to week 8, reported in a previously published study [11]. The mean and standard deviation (SD) of the mean percent change of inflammatory acne lesion counts were -32.4 ± 44 and -15.1 ± 44.9 for the active treatment and control groups, respectively. To achieve 80 % power (β = 0.20), a significance level of 0.05 (α) in a two-tailed test, calculated using Cohen's d effect size values for t-tests (0.39), 28 participants, based on an estimated 20 % dropout rate, are needed for each group. This results in a required total of 56 for the trial. The mean and SD of the mean percent change of inflammatory acne lesion counts from this pilot study will be used for recalculation of the sample size for larger trials.

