**Discussion:**

This trial will provide evidence regarding the inhibitory effect of CBT on inflammatory acne lesions and facial heat. The findings of this trial may have important implications for the more widespread use of CBT for the treatment of acne vulgaris.

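### The sample size of 28 per group does not give the stated 80% power at d = 0.39: power is about 30%, or 24% with 20% dropout

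*Protocol article*

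**What the plan says.** The Sample size section gives a complete calculation.

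- The endpoint is the "mean percent change of inflammatory acne lesion counts from baseline to week 8".
- The assumed values, taken from a published study, "were -32.4 ± 44 and -15.1 ± 44.9 for the active treatment and control groups, respectively".
- The design target is "To achieve 80 % power (β = 0.20") with "a significance level of 0.05 (α) in a two-tailed test", using a Cohen's d of 0.39 for t tests.
- The result is that "28 participants, based on an estimated 20 % dropout rate, are needed for each group", giving a total of 56.

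The Baseline data and outcome data section plans an independent t test for this endpoint, and the Randomization section specifies 1:1 allocation. The sizing therefore refers to the test that will be used.

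The Sample size section ends by treating the trial as preliminary: "The mean and SD of the mean percent change of inflammatory acne lesion counts from this pilot study will be used for recalculation" of the size of larger trials. Elsewhere the article does not treat it as a pilot. The Aim of the study section sets a superiority hypothesis on the primary endpoint. The abstract's discussion says "This trial will provide evidence regarding the inhibitory effect of CBT on inflammatory acne lesions and facial heat". The main Discussion lists an adequate sample size among the quality elements the authors considered.

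**The concern.** A standardised difference of 0.39 lies between what are usually called small and medium effects. At 80% power, a two-sided comparison of two means at that size needs about a hundred patients per group, so 28 per group including dropout stands out at once.

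This calculation is the only justification given for the number of patients, and it concerns the primary endpoint. If the power is far below 80%, a non-significant result is the likely outcome even when the assumed effect is real. A reader who trusts the stated power would be invited to take that result as good evidence against the treatment, which it would not be. The pilot label does not remove the problem, because the section still says that 28 per group are needed for 80% power.

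**Working it through.** **Inputs** (all from the Sample size section): means -32.4 and -15.1, SDs 44 and 44.9, two-sided alpha 0.05, power 0.80, dropout 20%, 28 per group.

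**1. Effect size.**
- Difference = 32.4 - 15.1 = 17.3 percentage points.
- Pooled SD = √((44² + 44.9²)/2) = 44.45.
- d = 17.3/44.45 = 0.389. The stated 0.39 is reproduced.

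**2. Sample size for 80% power.**
- Normal approximation: n per group = 2(1.960 + 0.842)²/d² = 2 × 7.85/0.39² = 103.2, so 104.
- Exact noncentral t: 104.2 (d = 0.39) to 104.6 (d = 0.389), so 105 evaluable per group.
- With 20% dropout: 105/0.8 = 131.25, so 132 per group, 264 in total. The normal approximation gives 104/0.8 = 130 per group.
- The stated 28 per group is not reproduced. It is short by a factor of 132/28 = 4.7.

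**3. Power at the stated size.** Power is the probability that a noncentral t variable with 2n - 2 degrees of freedom and noncentrality d√(n/2) exceeds the two-sided 5% critical value. After 20% dropout, 28 × 0.8 = 22.4, so about 22 per group remain.

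| Evaluable per group | Noncentrality (d = 0.389) | Power, exact t | Power, normal approximation |
|---|---|---|---|
| 28 | 0.389 × √14 = 1.46 | 0.299 | 0.307 |
| 22 | 0.389 × √11 = 1.29 | 0.243 | 0.252 |

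Using d = 0.39 instead changes the exact figures only to 0.300 and 0.244.

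**4. What the trial can detect with 80% power.**
- 28 per group: d = 0.762, and 0.762 × 44.45 = 33.9 points.
- 22 per group: d = 0.865, and 0.865 × 44.45 = 38.4 points.
- Both are about twice the assumed 17.3 points.

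**5. Expected precision.** The 95% confidence interval half-width is t × 44.45 × √(2/n).
- 28 per group: 2.005 × 44.45 × 0.267 = 23.8 points.
- 22 per group: 2.018 × 44.45 × 0.302 = 27.0 points.
- An observed difference equal to the planned one would give -17.3 ± 23.8, that is -41.1 to 6.5, which includes zero.

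**6. Could another reading give 28?**
- One-sided 5% test: 82 to 83 evaluable per group.
- Two-sided 10% test: 82 to 83 evaluable per group.
- 56 read as the number per group: power 53%.
- Power target lowered to 50%: 51 per group.
- One-sample or paired t test: 54 (two-sided) or 43 (one-sided).
- Effect size doubled to 0.78: 26 evaluable, 33 after dropout.
- Baseline adjustment: the required n is multiplied by 1 - r². To bring 104 down to between 28 and 22.4, r must be about 0.86 to 0.89. The article states no such correlation, and it sized a t test.

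None of these gives 28 per group.

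**The case against.** The arithmetic has no good defence, but several points on the other side deserve a hearing.

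**The trial is called a pilot.** A pilot may be small and need not be powered. That would excuse 56 patients, but not a sentence saying that 56 patients deliver 80% power.

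**The 24% figure may not describe the primary analysis.** The primary outcome is tested in the intention-to-treat set with last observation carried forward, so up to 28 per group could be analysed despite dropout. This stands: 24% is the figure for completers, and it follows the plan's own allowance for dropout. Nor is 30% assured, since carrying forward early values can dilute the effect. If, as an illustration, the mean difference shrank by 10% to 20% with unchanged SD, power at 28 per group would be about 25% to 21%.

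**The wording in the abstract and Discussion is generic.** A pilot also provides evidence, and the remark about sample size only lists what the authors considered. This is fair. Those phrases are consequences of the error, not separate errors.

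**The document nowhere says that non-significance will be read as no effect.** True. The misstated power invites that reading but does not prescribe it.

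**A 95% confidence interval is already planned.** Also true, so part of the remedy is in place. What is missing is a primary conclusion based on that interval.

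**Conclusion.** The concern holds. On the article's own inputs, 80% power needs 105 evaluable patients per group, or 132 per group after 20% dropout, against 28 stated. The actual power is about 30% if all 28 per group contribute and about 24% if only 22 do. Rounding and the choice of approximation move these figures by about one percentage point.

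The result assumes the printed means and SDs, 1:1 allocation and the unadjusted two-sample t test that the article specifies. It does not depend on the cited study, because every input is printed. The statement must be corrected, since it is the sole basis for the trial's size on its primary endpoint.

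**What to change.** If the size stays at 56, revise the Sample size section as follows:

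- Delete the claim of 80% power.
- Say that 56 is a pilot size, with about 30% power for d = 0.39 when 28 per group are analysed and about 24% for completers after 20% dropout.
- Give the expected 95% confidence interval half-width: about 24 points at 28 per group and 27 at 22.
- State that the primary conclusion will be the estimated difference with its 95% confidence interval, and that non-significance will not be read as absence of effect.

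Then bring the rest of the article into line. The superiority hypothesis in the Aim of the study section should match a pilot objective. The Discussion should no longer count sample size among the trial's strengths, and the promise of efficacy evidence there and in the abstract should be toned down.

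The cost is text only, with no extra patients and a less favourable stated power. Because the protocol has ethics approval and the basis for the primary conclusion changes, the sponsor should check whether the revision needs to be submitted; the article does not say.

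If the sponsor wants a confirmatory trial instead, the alternative is to resize to about 264 patients, which adds 264 - 56 = 208.
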